### Outcome measures

Various outcomes will be examined to assess the health profiles of individuals entering old age in rural and urban areas and to investigate the meaningful associations between healthy aging and the following four factors: biological factors, psychological factors, social factors, and KM-based phenotype factors [18–38]. Biological factors include sex, age, weight, height, BMI, blood pressure, pulse rate, body temperature, overall wellness, smoking and alcohol history, physical activity, nutritional status, dietary habits, appetite, supplement intake, constipation degree, comorbidities, daily living activities, physical resilience, oral and gynecological health, medical, surgical, and medication histories, family medical history, physical performance, knee and lumbar joint range of motion, core and grip strength, hearing, vision, pulmonary function, pulsometry, brain wave examination, bone density, body composition, and clinical lab tests, including biochemical, hormonal, hematological markers, urine tests, and omics profiles (metabolomics/lipidomics, proteomics). Psychological factors include assessments of overall wellness, sleep quality, quality of life, fear of falling, depression levels, and cognitive function. Social factors include education level, family and social relationships, pregnancy and lactation history, overall wellness, smoking and alcohol history, healthcare access, and quality of life. KM-based phenotype factors such as kidney deficiency, five organ deficiency, blood stasis, and core seven-emotions status will also be evaluated. Table 1 provides details of the measurements and instruments used in this study to be acquired.

**Table 1 pone.0316986.t001:** Measurement and instruments used in the Korean Medicine for Aging Cohort (KoMAC) study.

Category	Variables	Instruments and measurement	Visit
1. Sociodemographic	Sex, age, education level, family relationships, pregnancy and lactation history	Each factor will be collected using self-report.	1,2,3
2. Anthropometric parameters	Weight, height, body mass index	Each factor will be measured by BSM330. (InBody Co., Ltd., Korea)	1,2,3
3. Vital signs	Blood pressure, pulse rate, body temperature	Blood pressure, pulse rate will be measured by BPBIO320, InBody Co., Ltd., Korea) and body temperature will be determined by Non-contact forehead thermometer HFS-900. (HuBDIC Co., Ltd., Korea).	1,2,3
4. Health habits	Health habit about following 8 items will be measured; a. Overall wellness status b. Smoking and alcohol consumption history c. Quality of sleep d. Physical activity e. Nutritional status f. Dietary survey g. Appetite h. Social relationships	a. The Paving the Path to wellness questionnaire. b. The factor will be collected using self-report. c. Korean version of the Pittsburgh Sleep Quality Index, a subjective assessment of sleep quality over the past month, comprising 7 domains with a total of 18 questions. Scores range from 0 to 3, with higher scores indicating lower sleep quality [18]. d. The Korean Short Form of the International Physical Activity Questionnaire (IPAQ) records moderate-intensity physical activity, high-intensity physical activity, and walking performed over the past 7 days. The IPAQ score conversion guidelines are used to convert physical activity time into Metabolic Equivalent of Task (MET-min/week) scores [19]. e. The Mini Nutritional Assessment Short Form comprises 6 questions. With a total score of 14 points, a score of 12–14 indicates normal nutritional status, 8–11 suggests a risk of malnutrition, and a score of 0–7 signifies malnutrition [20]. f. To assess the overall quality of the participants’ diet, variables such as the frequency of dining out per week, companions during meals, nutritional education, and awareness of nutritional labeling are used in the dietary survey [21]. g. The Simplified Nutritional Appetite Questionnaire comprises 4 items rated on a 5-point scale, where lower scores indicate poor appetite status [22]. h. The Medical Outcomes Study-Social Support Survey is a questionnaire used to assess the nature and strength of social support among participants. It consists of a total of 19 questions rated on a 5-point scale, where higher scores indicate higher levels of social support [23].	1,2,3
5. Health service status	Accessibility of Healthcare Services	Unmet medical needs refer to the experience where individuals responded “yes” to the question, “In the past year, have there been times when you wanted to visit a hospital or clinic (excluding dental care) but could not?” This defines instances of unmet medical services (excluding dental care) as unmet medical needs [24].	1,2,3
6. Health condition	Following biological and psychological factors of health condition will be determined every year; a. Quality of life b. Intake of health supplements and symptom relief, personal satisfaction c. Degree of constipation d. Degree of depression e. Fear of falling f. Comorbidities g. Activities of Daily Living h. Physical resilience (The Physical Resilience Scale) i. Oral health status, gynecological history, medical history, surgical history, medication history and family medical history	a. The SF-12 comprises two domains: the Physical Component Score and the Mental Component Score. It consists of a total of 8 questions rated on a 5-point scale, where higher scores indicate better health [25]. The EuroQol Group developed the EuroQOL 5-Dimension 5-level, which includes the EQ-5D assessing health status across 5 dimensions, and the EQ-5D Visual Analog Scale questioning subjective health levels. Higher scores signify higher quality of life [26]. b. The self-report questionnaire will be used to assess the health supplement use and satisfaction of participants in this study. Participants will be asked to indicate whether they currently use any health supplements, and if so, and how satisfied they are with the effects of these supplements. c. The Constipation Assessment Scale developed by McMillan and Williams (1989) comprises 8 items rated on a 3-point scale. Higher scores indicate more severe constipation [27]. d. The Geriatric Depression Scale Short Form Korean Version is a 15-item shortened depression assessment tool. It considers a cutoff score of 8 points or higher to determine the presence of depression [28]. e. Korean Falls Efficacy Scale-International consists of 16 items, rated on a scale of 0 to 64, where a higher score indicates lower self-efficacy [29]. f. The Charlson Comorbidity Index (CCI) is based on a study conducted in 1984 at the New York Hospital, where the medical records of 604 patients hospitalized for one month were analyzed. It identified 19 conditions that predicted one-year mortality. Each condition is assigned a weighted score (1, 2, 3, 6 points) based on the relative risk of each illness. The sum of these weights comprises the CCI [30]. g. The Korean version of the Instrumental Activities of Daily Living comprises 10 areas, with each item scored from 3 to 4 points, totaling 37 points. Higher scores indicate greater functional impairment, suggesting an increased need for care [31]. h. The Physical Resilience Scale is a tool focusing on recovery related to illness, comprising 15 items. Scores range from 0 to 15, where higher scores indicate a higher level of resilience in recovery from illness [32]. i. Each factor will be collected using self-report.	1,2,3
7. Cognitive function	Cognitive function	Cognitive function will be determined by the Korean version of the Montreal Cognitive Assessment [33].	1,2,3
8. traditional KM questionnaire	The KM-based phenotype will be assessed by following questionnaire; a. Kidney deficiency b. Five Organ deficiency c. Blood stasis status d. The Core Seven-Emotions status	a. Kidney deficiency pattern assessment questionnaire, this questionnaire designed for this study will be employed to assess its validity [34]. b. Assessment using the Instrument of Korean Medical Pattern Identification and Functional Evaluation for Five Organ [35] c. Assessment using the Blood Stasis Questionnaires on metabolic syndrome [36] d. Assessment using the Core Seven-Emotions Inventory Short Form [37]	1,2,3
9. Physical function test	Physical function will be collected by following assessment; a. Physical performance b. Range of Motion for knee and lumbar joints assessment c. Core-muscle strength d. Grip strength e. Hearing f. Vision g. Pulmonary function h. Brain wave and pulsometry	a. The Short Physical Performance Battery consists of three components: balance tests (side-by-side stand, semi-tandem stand, tandem stand), gait speed (4-meter walk), and chair stands (5 repetitions). Each section is scored out of 4 points, contributing to a total score of 12 points [38]. b. To assess the range of motion of the knee joint, the flexion and extension of the knee joint are measured using a goniometer. To assess the range of motion of the lumbar spine, the flexion and extension of the lumbar spine are measured using an inclinometer. c. To perform McGill’s core endurance test, the following tests are performed sequentially: isometric endurance test, flexor endurance test, extensor endurance test, and side bridge test. d. After confirming the dominant hand, the left and right grip strength is measured two set, three times each, at three-minute intervals, using the TKK-5401 (TAKEI Scientific Instruments Co.,Ltd., Japan). e. Using the GSI-18 (GRASON-STADLER INC., America), the minimum audible range of hearing in the left and right ear is evaluated by presenting sounds from 1000Hz to 4000Hz. f. The vision test will use the Snellen eye chart to examine the left and right vision. g. Pulmonary function tests were conducted using a Spirometer SB80B (Contec Medical Systems Co., Ltd., China). h. Brain waves and pulsometry will be measured using OMNIFIT Mindcare medical (BICO CO., LTD., Korea), and HRV, brain score, brain activity, brain stress, brain imbalance, and concentration will be evaluated.	1,2,3
10. Body composition measurements	Bone density, body composition	Bone density and body composition is will be measured by using QDR 2000 Densitometer Machine (Hologic Inc., America) and Inbody 770 (InBody Co., Ltd., Korea), respectively.	1,2,3
11. Clinical laboratory	• Blood test a. Biochemistry b. Hormone c. Hematology • Urine test • Omics test e. Metabolomics/lipidomics f. Proteomics	The blood test will be performed using a QDR 2000 densitometer machine (Hologic Inc., America). a. The biochemistry will be used to check the levels of Albumin, AST, TP, Total bilirubin, Ca, Cl, Pi, Na, ALP, Amylase, CK, ALT, LDH, γ-GTP, BUN, Creatinine, Uric acid, Total cholesterol, HDL cholesterol, Triglyceride, LDL cholesterol, and Glucose through blood analysis. b. The hormones to be checked are 25-OH Vitamin D, Osteocalcin, Cortisol, Free T4, TSH, DHEA-S, Vitamin B12, Insulin, GDF8, GDF15, Testosterone, PSA, FSH, LH, and Estradiol. c. The hematology test will check the following: white blood cells, red blood cells, hemoglobin, hematocrit, platelets, mean corpuscular volume, mean corpuscular hemoglobin, mean corpuscular hemoglobin concentration, neutrophils, lymphocytes, monocytes, eosinophils, basophils, and glycated hemoglobin. d. We will be checking the following items in a urine test: Urine WBC, Specific gravity, pH, Protein, Glucose, Occult Blood, Ketones, Urobilinogen, Bilirubin, Nitrite, WBC, RBC, Epithelial cell, Bacteria, Casts, Crystal, Other e. GC/LC-MS based untargeted metabolomics analysis will be conducted to profile the comprehensive metabolic data from blood of participants f. Beads-based multiplex immunoassay will be executed to acquire the proteomics data of blood	1,3

Biological factors: sex, age, weight, height, body mass index, blood pressure, pulse rate, body temperature, overall wellness status, smoking and alcohol consumption history, physical activity, nutritional status, dietary survey, appetite, intake of health supplements, degree of constipation, comorbidities, activities of daily living, physical resilience, oral health status, gynecological history, medical history, surgical history, medication history and family medical history, physical performance test, range of motion assessment for the knee and lumbar joints, core muscle strength measurement, grip strength measurement, hearing, vision, pulmonary function, pulsometry, brain wave examination, bone density, body composition, clinical laboratory examination (biochemical markers, hormones, hematological markers, urine test), and omics profiles (metabolomics/lipidomics, proteomics).

Psychological factors: overall wellness status, quality of sleep, quality of life, fear of falling, degree of depression, and cognitive function. Social factors: education level, family relationships, pregnancy and lactation history, overall wellness status, smoking and alcohol consumption history, social relationships, accessibility of health care Services, and quality of life. KM-based phenotype factors: kidney deficiency, five organ deficiency, blood stasis, and core seven-emotions status.

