### Study sample

This study will be conducted with a target group of 1000 participants who are entering old age and who are recruited from Wonkwang University Korean Medicine Hospital, a medium-sized city, and Jangheung Integrative Medical Hospital, a rural area in South Korea. The objective is to investigate potential cohort losses due to yearly mortality and other factors, with a target panel retention rate exceeding 80%. Despite limitations in achieving perfect representativeness of the population, practical feasibility will be considered by selecting research participants based on the demographic distribution of the population aged 50–65 years in Iksan and Jangheung, Jeonbuk, as of 2023 [16,17]. Considering the budget for this cohort project and the target population of individuals entering old age at Iksan and Jangheung in 2023 (for a total of 82,498 individuals), the goal is to recruit approximately 1% of this target population while factoring in a panel dropout rate of 20%. Therefore, the aim is to register a total of 1,000 adult participants, encompassing both sexes.

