### Study population

This study will be This proposal involves recruiting 1,000 individuals over a two-year period from August 2023 to December 2024 for the study of individuals entering old age. Eligible participants will be identified by Clinical Research Coordinators (CRCs) from each institution who receive thorough training regarding the inclusion/exclusion criteria and recruitment procedures.

The inclusion criteria are as follows: (1) adults aged 50 to 65 years; (2) adults residing in either a medium-sized city (Iksan city and nearby areas in Jeonbuk state) or a rural area (Jangheung County and nearby areas in Jeonnam state); (3) adults who can read and respond to the questionnaire; and (4) adults who understand the purpose of the study and provide written consent to participate. The exclusion criteria are as follows: (1) a history of major psychiatric disorders diagnosed by the DSM-5, such as psychotic symptoms, schizophrenia spectrum disorders, delusional disorders, bipolar disorders, alcohol or substance use disorders; (2) the inability to communicate effectively or limitations in reading and writing; and (3) determination by the research team or responsible personnel that the study cannot be completed due to a medical condition. Additionally, (1) participants for whom the selected or excluded criteria are violated following screening, (2) participants who withdraw consent during the study, and (3) participants who are not traceable will be considered premature withdrawals from this study.

After registration, follow-up examinations will be performed at 1-year intervals from August 2024 to December 2025. However, blood tests will be administered every two years: at baseline and during the final follow-up. A strategy for sustained participation will be adopted to keep participants engaged in the cohort study. This will include sending quarterly health management information through a webzine and providing free health consultation services to prevent dropout of participants. Additionally, substantial compensation will be provided every visit, along with immediate explanations of the health screening process, to minimize participant attrition.

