### Statistical analysis

We will conduct various analyses within the cohort. The results of the participants’ demographic data, the questionnaire-based prevalence of age-related symptoms and KM-based phenotype, physical function, and other outcome variables will be summarized using descriptive summary measures. For continuous outcomes, both univariate and multivariate linear regression analyses will be employed, while logistic regression will be used for dichotomous outcomes. Specifically, group differences (between KM-based phenotypes or between rural and urban areas) will be analyzed using Student’s t test and analysis of variance. The relationships between KM-based phenotypes and physical and psychological health, as well as demographic variables, will be analyzed using multiple regression.

Additionally, missing data patterns will be examined, and appropriate methods for handling missing data, such as Last Observation Carried Forward (LOCF) or Multiple Imputation, will be applied. Mixture models will be utilized to identify subgroups of subjects based on their biological and psychological characteristics. To estimate the cumulative risk of outcomes, Kaplan‒Meier analysis will be employed. Adjustments for covariates will be made before the follow-up period, during which Cox proportional hazard models will be used to estimate the risk of experiencing any of the outcomes. In addition, prediction modeling will be attempted by incorporating new covariates under investigation. P values less than 0.05 will be considered to indicate statistical significance. All statistical analyses will be conducted using SAS® version 9.4.

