## Discussion

South Korea is currently navigating the challenges of transitioning into a super-aged society, emphasizing the critical importance of proactive health management for healthy aging before individuals reach the age of 65 years [1–5]. This paper outlines a multifaceted research protocol aimed at revealing the complexities associated with aging in both urban and rural settings, considering the distinctive characteristics that are prevalent in various regions of Korea. Data collection for this study began in August 2023 and is being carried out in two phases. Phase I comprises a cross-sectional cohort study (baseline) detailed in this paper. Participants who are included in the cohort will be given the option of allowing their data to be used for analyses and identifying them for future research interventions or for comparison purposes for intervention trials. Details of the phase II interventions will be published in full manuscripts separately.

In particular, a key aspect of our study involves analyzing KM-based phenotypes to examine aging patterns and certain diseases associated with each phenotype and evaluating the KM-based integrated health management model. To achieve this goal, in phase I, our initial focus is on identifying diagnostic markers that enable the application of KM by conducting multi-omics analyses, including hormone, immune, metabolite markers. We will subsequently explore age-related symptoms or vulnerable diseases associated with KM phenotypes through cohort studies. In phase II, we plan to conduct multiple randomized controlled trials that apply interventions such as community programs specifically tailored to well-defined KM-based phenotypes identified in phase I to verify the effects of KM on healthy aging. Based on these results, we intend to develop an integrated health management model for healthy aging, and establish a comprehensive database and blood biobank of population entering old age in rural and urban areas of Korea.

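### The test named for differences between KM phenotypes is unadjusted, so in a mixed-sex cohort a sex hormone could pass as a phenotype marker

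*Protocol article*

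**What the plan says.** All references are to the protocol article.

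- **Aim.** For phase I, the Discussion says that "our initial focus is on identifying diagnostic markers that enable the application of KM by conducting multi-omics analyses, including hormone, immune, metabolite markers". The abstract and the Results section also make phenotype markers the focus of the baseline phase.
- **Panel.** The hormone list in Table 1 (Outcome measures, item 11, Clinical laboratory) ends with "Testosterone, PSA, FSH, LH, and Estradiol". No restriction to men or women is attached.
- **Sample.** Study sample: "the aim is to register a total of 1,000 adult participants, encompassing both sexes". No sex ratio or quota is given. Study population admits "adults aged 50 to 65 years".
- **Phenotypes.** Table 1, item 8, assesses them with four questionnaires: kidney deficiency, five organ deficiency, blood stasis and core seven emotions.
- **Analysis.** Statistical analysis first gives a general rule of univariate and multivariate linear regression for continuous outcomes. It then narrows: "group differences (between KM-based phenotypes or between rural and urban areas) will be analyzed using Student’s t test and analysis of variance". The next sentence is "The relationships between KM-based phenotypes and physical and psychological health, as well as demographic variables, will be analyzed using multiple regression". Covariate adjustment is mentioned once more, next to the Cox models for follow-up. No covariate is named anywhere.
- **Data collected.** Sex and age are in Table 1, item 1. Gynecological history is self-reported under item 6. Menopausal status is not named.

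**The concern.** Phenotype groups formed from questionnaire answers are not randomised, so nothing makes them alike in sex or reproductive stage. The section itself plans to relate phenotype to demographic variables, so it treats an association between phenotype and sex as an open question. A t test or ANOVA on a hormone asks only whether group means differ. If one phenotype is commoner among women, a hormone whose level depends on sex will differ between the groups even when it has no link to the phenotype within either sex.

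The section names two kinds of analysis that can give different answers for the same hormone, and it does not say which one counts. The method it ties specifically to phenotype differences is the unadjusted one. At stake is the credibility of the phase I marker list: some entries could be proxies for sex.

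**Working it through.** The article gives no power or error-rate figure on this point, so there is none to reproduce. Only its total of 1,000 and its significance level of 0.05 (taken as two-sided) enter below.

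**Assumptions, none given in the article**
- n per group: 500 (1,000 split in two), with 300 as a variant.
- d: the difference in analyte between women and men, in within-sex SD: 1, 2 or 3.
- Δp: the difference between the phenotype groups in the share of women.
- True effect of phenotype on the analyte within sex: zero.
- About half the sample are women.

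**Formula**

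The spurious mean difference is d × Δp. With about 50% women the pooled SD is √(1 + d²/4). So

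z = d × Δp / [√(1 + d²/4) × √(2/n)],

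and the rejection rate is approximately Φ(z − 1.96).

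**Two groups of 500, Δp = 0.10** (√(2/500) = 0.0632)
- d = 2: SD = √2 = 1.414; z = 0.20/(1.414 × 0.0632) = 2.24; rate Φ(0.28) = 0.61.
- d = 3: SD = √3.25 = 1.803; z = 0.30/(1.803 × 0.0632) = 2.63; rate Φ(0.67) = 0.75.

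**Variants by the same formula**

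| n per group | Δp | d = 2 | d = 3 |
|---|---|---|---|
| 500 | 0.10 | 0.61 | 0.75 |
| 500 | 0.15 | 0.92 | 0.98 |
| 300 | 0.10 | 0.41 | 0.53 |

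**Check by simulation** (1,500 runs per setting, N = 1,000, 30% of participants in the phenotype, 50% women in the comparison group)

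| Women in phenotype | t test, d = 1 | t test, d = 2 | t test, d = 3 | Regression with sex, d = 1 to 3 |
|---|---|---|---|---|
| 50% | 5% | 5% | 5% | 4–5% |
| 55% | 11% | 18% | 22% | 5% |
| 60% | 26% | 52% | 69% | 4–6% |
| 70% | 73% | 99% | nearly 100% | 5–6% |

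With an equal split and 60% v 50% women, the simulated t test rejected in 62% (d = 2) and 74% (d = 3) of runs, in line with the formula. The simulation error on a 5% rate is √(0.05 × 0.95/1,500) = 0.6 percentage points, so the adjusted rates are consistent with the nominal level.

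**The case against.** The strongest reply is that the plan already contains the remedy. Statistical analysis applies multivariable linear regression to continuous outcomes, and the Outcome measures section lists hormones and omics profiles among its measures. On a plain reading that regression covers them, and sex and age head the list of sociodemographic variables. Which covariates go into which model is detail that a condensed article may leave to the full protocol or analysis plan.

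Much of this stands. A missing covariate list is not an error here, and it would be wrong to say that regression is excluded for laboratory markers. What remains is a choice the article does state: it specifically ties phenotype differences to the t test and ANOVA, and it does not let the adjusted result decide.

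A reader might infer more in three places, and the article does not support it:
- **Pooling as settled fact.** Nowhere does it say that men and women will be pooled for the hormone comparisons. It says neither that nor the opposite.
- **Markers that define the phase II groups.** Phenotypes are assessed by questionnaire. The Discussion says phase II interventions are tailored to phenotypes identified in phase I and that their details will be published separately. It does not say that a hormone or omics result decides who receives what.
- **Menopausal status as a variable in hand.** Only gynecological history is listed.

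It is also fair to object that the size rests wholly on assumptions. A sex difference of 2 to 3 SD is assumed for sex hormones and says nothing about the typical metabolite or protein. Finally, compulsory adjustment of every marker for age or menopause could remove signal that a study of aging wants to see.

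**Conclusion.** The point holds in a limited form. The test expressly named for phenotype differences is unadjusted, the marker search includes hormones that depend on sex, and the article does not say that an adjusted analysis takes precedence. If the phenotype groups differ in sex mix and the unadjusted result is used, the false-positive rate for a hormone that only tracks sex is well above 5%. It is about 61% to 75% with two groups of 500, a 10-point imbalance and a 2 to 3 SD sex difference. It is about 11% with 30% of 1,000 in the phenotype, a 5-point imbalance and a 1 SD difference. With no imbalance it is 5%.

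The imbalance, the sex effect and the group sizes are all assumed, so these rates show what could happen and do not forecast it. The article does not show that the error will occur, since the planned regression may include sex. The change is worth making because it settles in advance which result counts, and because the key variable, sex, is already recorded.

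**What to change.** In Statistical analysis:

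1. Make the sex-adjusted regression the basis for declaring a phenotype marker, and keep the t test and ANOVA as descriptive.
2. Analyse testosterone, PSA, FSH, LH and estradiol within sex. For these five a single sex term may not be enough, because spread and any relation to phenotype can also differ between men and women.
3. In women, report FSH, LH and estradiol by menopausal status, if the gynecological history records it. Confirm this on the case report form first.
4. Show marker results with and without age adjustment, because aging is itself under study. Compulsory adjustment of every marker for age and menopause is not needed.

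The cost is a few sentences, with no new data for items 1, 2 and 4. Within-sex tests use about half the sample if the sexes are roughly equal in number, so they have less power, and a menopausal split in women reduces it further.
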